#### Stopping rule

The effect of the treatment will be assessed by measuring how many people get vaccinated at the seven public vaccination events on 2021-11-13, 2021-11-19, 2021-11-20, 2021-11-26, 2021-11-27, 2021-12-10, and 2021-12-11.

#### Variables

##### Manipulated variables

The treatment group will receive a letter from the mayor of the city inviting them to get a COVID-19 vaccination at one of seven public vaccination events. The letter offers two financial incentives. If the recipient is not already vaccinated and gets vaccinated at the vaccination events, they will receive 20 Euros (in the form of a shopping voucher). Additionally, another 20 Euro incentive is offered if more than 900 city residents get vaccinated at one of the seven vaccination events. If the recipient is already vaccinated, they can still get the second incentive if they give the treatment letter to someone else and that individual brings it to one of the seven vaccination events, gets vaccinated, and more than 900 city residents get vaccinated during the one of the seven vaccination events. The control group will get the same letter as the treatment group but without the offer of monetary incentives.

##### Measured variables

**Primary measures:** Information uptake is measured by whether a participant visited the informational website mentioned in the letter (unique website visits). The website is prominently displayed in both treatment and control letters. Each URL and QR-code is unique to the individual recipient. Vaccination uptake is measured via an on-site record of administered vaccinations during the seven public vaccination events. The records will distinguish between primary vaccines (i.e., first and second doses) and boosters. **Covariate measures:** These data will be collected from municipal administrative records and will be used as covariates to increase precision - Age - Sex - Indicator for whether the individual is a non-German national. **Additional measures:** To determine an individual's close social network, we use address data from municipal administrative records to identify shared addresses and generate unique clusters. As an alternative specification, we use shared last name and shared address to generate a secondary cluster id. The treatment letters given to other residents by fully-vaccinated treatment letter recipients will be collected at the public vaccination events to track which

subjects were referred to get vaccinated by the treatment-letter recipient. We will also collect information (self-reports) whether patients are part of a vulnerable high-risk group which the German federal government prioritizes in the vaccine distribution.

### **Analysis Plan**

#### Statistical models

We will use OLS regression with a treatment indicator, block fixed effects, and control covariates (consisting of a binary indicator for female, an indicator for non-German nationality, age, and age squared) in all subsequent analyses unless indicated otherwise. To ensure robustness, a secondary analysis will regress outcomes against the treatment indicator without controls. H1-1 (direct or “total” effect #1): Information uptake regressed against treatment group for only cluster representatives, with robust standard errors. H1-2 (direct or “total” effect #2): Vaccination uptake regressed against treatment group for only cluster representatives, with robust standard errors. H2 (spillover effect): Vaccination uptake regressed against treatment group for all individuals who are not cluster-representatives, with robust clustered standard errors. H3-1 (overall effect #1): Information uptake regressed against treatment group for all individuals, with robust clustered standard errors. H3-2 (overall effect #2): Vaccination uptake regressed against treatment group for all individuals, with robust clustered standard errors.

#### Inference criteria

We will use p-values (threshold = 0.05) associated with the treatment indicator coefficient in our regressions.

#### Data exclusion

Aside from the exclusion of the two largest clusters, since we use block fixed effects, the one subject in a single-person household that was randomly determined to be in a block size of one will be dropped from analysis.

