### Design Plan

Study type

Experiment

Blinding

No blinding is involved in this study.

Study design

The design is a blocked, two-stage (individual and household) randomized controlled field experiment.

Randomization

The study will be conducted in a medium-sized city in Germany. Treatment assignment follows a two-stage randomization process. In the first stage, all housing addresses within the city will be randomized into two groups (i.e., intervention group and control group), blocked by household size. In the second stage, one resident of each address in both groups will be randomly selected (a "cluster representative"). The cluster

representatives in the intervention group only will be sent the intervention letter. All remaining residents will be sent the control letter. The randomization will be conducted in R (version 4.1.1) using the function “sample” with the seed set to 2021.

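### Blocks look finer than household-size strata but their size is not given; if they are small, ordinary address-clustered standard errors make the H2 and H3 tests too liberal

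*Protocol*

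**What the plan says.** - **Blocking.** Design Plan, Randomization: addresses are "randomized into two groups (i.e., intervention group and control group), blocked by household size". The number of addresses per block is not given. The Research design section describes two groups of equal size.
- **Exclusion.** Data exclusion: because block fixed effects are used, "the one subject in a single-person household that was randomly determined to be in a block size of one will be dropped from analysis".
- **Model.** Statistical models: "We will use OLS regression with a treatment indicator, block fixed effects, and control covariates". This applies to all hypotheses unless stated otherwise.
- **Standard errors.** For the direct effect on vaccination (H1-2): "Vaccination uptake regressed against treatment group for only cluster representatives, with robust standard errors". For the overall effect (H3-2): "Vaccination uptake regressed against treatment group for all individuals, with robust clustered standard errors". H2 is worded like H3, on residents who are not cluster representatives. Neither the clustering level nor the estimator variant is named.
- **Cluster.** Measured variables: address records are used "to identify shared addresses and generate unique clusters".
- **Decision rule.** Inference criteria: "We will use p-values (threshold = 0.05) associated with the treatment indicator coefficient in our regressions".
- **Sample.** 41,549 residents at 10,033 addresses.

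**The concern.** The two descriptions of the blocks do not match. If a block were a whole household-size stratum, the single-person stratum could be a block of one only if the city had a single such address, which is implausible among 10,033. Chance would not decide it either. The exclusion fits a scheme in which addresses were cut into blocks of some fixed size, with one address left over.

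The right standard error depends on that size. Fixed effects for small blocks force the residuals of addresses in the same block to offset each other. An ordinary sandwich variance summed over addresses ignores this and comes out too small. The p-value at 0.05 is the only inference criterion, and effects within address clusters, tested by H2, are presented in the background section as the research gap. A variance that is too small would produce false claims of spillover.

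**Working it through.** **1. The plan's own figure.** The protocol states about 80% power for effects of 2.6 (direct), 1.5 (spillover) and 1.3 (overall) percentage points. Inputs: 20% ineligible, control rate up to 20%, 1:1 allocation, alpha 0.05 taken as two-sided. Among eligible persons:

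- Direct: 10,033 × 0.8 / 2 ≈ 4,013 per arm, 20.0% v 22.6%: power 81.2%.
- Spillover: (41,549 − 10,033) × 0.8 / 2 ≈ 12,606 per arm, 20.0% v 21.5%: 83.6% before clustering. With an assumed ICC of 0.03 (design effect 1 + 2.14 × 0.03 = 1.064): 81.2%.
- Overall: 41,549 × 0.8 / 2 ≈ 16,620 per arm, 20.0% v 21.3%: 83.3% before clustering. With ICC 0.03 (design effect 1 + 3.14 × 0.03 = 1.094): 79.9%.

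The power statement reproduces, for a test whose true size is 5%.

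**2. Which block sizes fit.** If one block size k was applied over all 10,033 addresses and one was left over, k divides 10,032 = 2⁴ × 3 × 11 × 19. Sizes 2, 3, 4, 6, 8, 11, 12 and 16 all qualify, among others. The protocol does not single out pairs.

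**3. Variance ratio.** Take P pairs with within-pair differences d and estimate β, the mean of d. Each address residual is ±(d − β)/2. With S = Σ(d − β)², the uncorrected address-level sandwich (HC0/CR0) gives S/(2P²), while the true variance is about S/P². The ratio is 0.50. For k addresses per block it is 1 − 1/k.

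The usual correction (CR1) multiplies this by about (N − 1)/(N − K), where K is roughly the number of blocks. With 41,549/10,033 = 4.14 residents per address, the CR1 ratio is (1 − 1/k) / (1 − 1/(4.14k)). For pairs: 0.50 / (1 − 1/8.28) = 0.569.

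True size of the nominal 5% test = 2 × [1 − Φ(1.96 × √ratio)].

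| k | CR0 ratio | CR0 size | CR1 ratio | CR1 size |
|---|---|---|---|---|
| 2 | 0.50 | 16.6% | 0.569 | 13.9% |
| 4 | 0.75 | 9.0% | 0.798 | 8.0% |
| 8 | 0.875 | 6.7% | 0.902 | 6.3% |
| 16 | 0.938 | 5.8% | 0.952 | 5.6% |

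For H2 with pairs, N = 31,516 and K ≈ 5,017, so the correction is 31,516/26,499 = 1.19, the ratio 0.59 and the size about 13%.

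**4. Simulation** (4,000 null replicates, 10,032 addresses of 4 residents, 16% rate, ICC 0.05; rate, ICC and equal address size are assumptions).

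| k | CR0 | CR1 | CR2 | Clustered on block |
|---|---|---|---|---|
| 2 | 16.7% | 14.1% | 5.3% | 5.3% |
| 4 | 8.7% | 7.7% | 4.8% | 4.9% |
| 8 | 6.5% | 6.2% | 4.9% | 4.9% |
| 1,672 (six strata) | 4.9% | 4.9% | 4.8% | 10.2% |

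**5. H1.** With one representative per address and pairs, N = 10,032 and K = 5,017. The HC1 factor is 10,032/5,015 ≈ 2.0, which cancels the 0.50. Simulated size for pairs was 5.4% with HC1 or HC2 and 17.0% with HC0.

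**The case against.** The strongest reply is that the inflation rests on three things the protocol does not state: the block size, the clustering level and the estimator variant. That stands, so the size can only be given as a range. The variant could also properly be settled in an analysis plan that is not shown. The block definition is different: it belongs to the randomisation design, which this document describes in two ways that do not agree, and the fixed effects and type of standard error are already fixed here.

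Four stronger readings are tempting and are not supported:

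- **That the plan runs its tests at about 16%.** This needs both pairs and an uncorrected estimator. Neither is stated, and blocks of four or eight fit the single left-over address equally well. Pairing separately within each household size is doubtful too: it would leave one address over in every size with an odd count, yet only one is dropped.
- **That H1 is invalid.** It is not under HC1 or HC2, which hold about 5% even with pairs.
- **That standard errors will be clustered on surname within address.** The protocol says "we use shared last name and shared address to generate a secondary cluster id", but Exploratory analysis uses it only as another definition of the social network.
- **That clustering on the block is always safe.** With six large strata it gives about 10%, against about 5% for address-level clustering.

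**Conclusion.** The point holds in conditional form, for H2 and H3. Data exclusion implies blocks finer than the household-size strata of the Design Plan, and the block size is missing. If blocks are small and the standard errors are the ordinary address-clustered kind, the 0.05 rule is too liberal: about 14% for pairs, 7–8% for blocks of four and 6–6.5% for blocks of eight with the usual correction (about 17%, 8–9% and 7% without it). Every small block size errs in the same direction. If blocks are large, the problem vanishes.

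These figures assume clustering on address, similar address sizes within a block, equal variance in the two arms, no variation of the effect between blocks, a two-sided test and a normal reference distribution.

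**What to change.** - State the number of addresses per block and how blocks were formed, and reconcile Design Plan with Data exclusion.
- For H2 and H3, name the clustering level and variant: CR2 clustered on address. Clustering on the block is an alternative only once it is confirmed that there are many small blocks; it should not be used for a few large strata.
- For H1, name HC1 or HC2.
- Check the H2 and H3 p-values by randomisation inference that re-runs the blocked assignment code over many draws.

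The cost is a few lines of text and code. Standard errors for H2 and H3 widen to their proper size. With pairs this is by 1/√0.569 − 1 ≈ 33% relative to CR1, or √2 − 1 ≈ 41% relative to the uncorrected form. With blocks of eight it is 1/√0.902 − 1 ≈ 5% relative to CR1, and with large blocks almost nothing.

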#### Exploratory analysis

For the analysis, all residents living at the same address will be treated as members of the same social network. We will test an alternative operationalization of a social network by considering all residents with the same last name who reside in the same address cluster as members of the same social network. We will also explore whether the hypothesized effects differ by German vs. non-German nationals. To better map out social influence, we will also compare which letters were given to individuals living in the same address as the treatment-letter recipient, which were given to individuals in the same address with the same last name, and which were given to individuals at a different address. Additionally, we will conduct analysis restricted to 1) first doses

(excluding second doses and booster shots), 2) first and second doses (excluding booster shots), and 3) boosters (excluding first and second doses). To explore whether the treatment effects in H1-2, H2, and H3-2 are driven by an increase in booster shots, we will perform the analyses as described in H1-2, H2, and H3-2 but using a multinomial logistic regression with no record of vaccination equal to zero, primary vaccination equal to 1, and booster vaccination equal to 2. A Wald test will be used to determine if the treatment coefficient in terms of primary vaccination is statistically significantly different from that of boosters.

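### The exploratory Wald test compares proportional increases in primary and booster uptake, so it does not in general show whether the percentage-point effects come from boosters

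*Protocol*

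**What the plan says.** Under Exploratory analysis the Protocol sets the question: "To explore whether the treatment effects in H1-2, H2, and H3-2 are driven by an increase in booster shots". The method follows: "we will perform the analyses as described in H1-2, H2, and H3-2 but using a multinomial logistic regression". The outcome has three categories, coded by dose type, and the two treatment coefficients are then compared: "A Wald test will be used to determine if the treatment coefficient in terms of primary vaccination is statistically significantly different" from the booster coefficient.

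The three hypotheses are specified under Statistical models: "We will use OLS regression with a treatment indicator, block fixed effects, and control covariates", to apply "in all subsequent analyses unless indicated otherwise". Robust standard errors are used for H1-2 and robust clustered ones for H2 and H3-2. The sample size rationale states the detectable effects in percentage points: 2.6 direct, 1.5 spillover and 1.3 overall.

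Randomisation is "blocked by household size". The number and size of blocks are not stated. Data exclusion, however, drops "the one subject in a single-person household that was randomly determined to be in a block size of one".

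Just before the multinomial model, the same section plans separate analyses of first doses, of first and second doses together, and of boosters.

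**The concern.** The effects to be explained are OLS coefficients, that is, differences in the percentage vaccinated. Asking whether boosters drive them means asking which dose type supplies the added vaccinations. The Wald test compares two log relative-risk ratios. The two comparisons agree only if primary and booster uptake have the same base rate.

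The second problem is how blocks enter. The text changes the link function and drops nothing from the right-hand side, so the logit carries the block fixed effects. These are harmless in OLS. In a maximum-likelihood logit, many small blocks bias the slopes away from zero, and blocks in which everyone has the same outcome contribute nothing.

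At stake is the reading of the trial on a policy point: whether the vouchers moved people who had no primary vaccination or mainly people seeking a booster. A non-significant Wald test could be taken to mean that boosters are not the source when they supply most of the gain.

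**Working it through.** **Inputs.** From the Protocol (Sample size and its rationale): 10,033 addresses, 41,549 residents, control uptake up to 20%, 20% ineligible, alpha 0.05 (taken as two-sided), about 80% power. Equal arms are stated in the project description. Assumed, because not given: the primary/booster split of the 20%, and the block size.

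**The plan's own figure.** Eligible representatives per arm: 10,033 × 0.8 / 2 ≈ 4,013. For 20% against 22.6%, SE = √[(0.20×0.80 + 0.226×0.774)/4,013] = 0.00914, z = 0.026/0.00914 = 2.85, power = Φ(2.85 − 1.96) ≈ 81%. Ignoring clustering, the same formula gives about 84% for spillover and 83% for overall; a design effect of 1.1 brings both to about 80%. The stated power is reproduced, so these inputs serve for the next step.

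**What the Wald contrast measures.** Let p and b be the primary and booster rates, with subscript 1 for intervention and 0 for control. The no-vaccination category cancels:

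β_primary − β_booster = ln(p₁/p₀) − ln(b₁/b₀), with variance (1/n)(1/p₀ + 1/p₁ + 1/b₀ + 1/b₁).

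The null is therefore equal relative risks. Under it, boosters supply the share b₀/(p₀ + b₀) of the gain, which is simply their share of the base rate.

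**Direct effect of 2.6 points, n = 4,013 per arm:**

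| Assumed control split, primary/booster | Booster share of gain when the Wald null is true | Rejection if the gain is half and half | Rejection if the gain is all boosters |
|---|---|---|---|
| 2%/18% | 90% | 82% (primary coefficient larger) | 13% |
| 4%/16% | 80% | 41% (primary coefficient larger) | 23% |
| 6%/14% | 70% | 18% (primary coefficient larger) | 35% |
| 10%/10% | 50% | 5% | 66% |

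Worked case, 4%/16% with all of the gain from boosters: contrast = ln(1) − ln(0.186/0.16) = −0.151; SE = √[(25 + 25 + 6.25 + 5.38)/4,013] = 0.124; z = −1.22; rejection about 23%. For the overall effect (1.3 points, about 16,620 per arm, clustering ignored) the figure is about 25%.

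Worked case, 2%/18% with boosters supplying 60%: primary goes to 3.04% and booster to 19.56%. The coefficients are 0.452 and 0.116, and the test rejects about 59% of the time with primary larger, although boosters supply more than half.

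**Same case on the percentage-point scale.** The contrast of the two risk differences is 0 − 2.6 = −2.6 points. The per-person variance of (primary indicator − booster indicator) is p + b − (p − b)²: 0.20 − 0.12² = 0.1856 in control and 0.226 − 0.146² = 0.2047 in intervention. SE = √[(0.1856 + 0.2047)/4,013] = 0.00986, z = −2.64, rejection about 75%, against 23% at the same assumed 4%/16% split.

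**Block fixed effects.** There were 200 simulated trials per setting, with about 10,032 representatives, a 4%/16% split, one set of dummies per block, and a true contrast of 0.50 (all of the gain primary):

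| Addresses per block | Mean estimated contrast | Blocks with no variation in outcome |
|---|---|---|
| 2 | 1.00 | 65% |
| 4 | 0.67 | 38% |
| 10 | 0.57 | 9% |
| 50 | 0.51 | 0% |

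The exclusion of one single-person household as a block of one implies blocks finer than household-size strata, since a stratum of all single-person households would not have size one. It does not fix the size.

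**The case against.** The case against has several parts, and much of it stands.

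- *The plan already holds a better answer.* The dose-specific analyses in the same section fall under the OLS default and would give percentage-point effects for each dose type. A reader might infer that the Wald test is the plan's only formal check, or that the plan cannot answer the question. The documents do not support that. What remains is that no comparison of those effects is planned, and that restricting an analysis to one dose type could be read as dropping people vaccinated with another, which would condition on the outcome.
- *The split is assumed.* True. At 10%/10% the test agrees with the percentage-point comparison, so the size of the problem is a range and not a single figure.
- *Relative increase is a legitimate question.* It is, but it is not the one posed, which concerns the source of effects estimated in percentage points. A test of equal risk differences has its own limit: its null is a half-and-half split. The two estimates with their intervals should therefore carry the conclusion.
- *Rejection with primary larger is not in itself false.* When the gain is half and half, it rightly says that boosters did not rise more in proportion. It misleads only if read as showing that primary doses supplied most of the gain.
- *The block argument is conditional.* Correct. A reader might infer that the model would fail to converge. The simulations returned finite estimates even for pairs, so this is not shown. Under equal true coefficients (0.155 each) both inflate together in pairs (0.33 and 0.31). The roughly 16% false rejection seen there used model-based standard errors, so it is not the error rate of the planned robust test.

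**Conclusion.** The point holds in a limited form. The Wald test answers whether primary and booster uptake rose by the same proportion. It answers the stated question only if the two base rates are about equal, and the Protocol gives no split. Across the splits tried, its null coincides with a booster share of the gain between 50% and 90%. At 4%/16% it detects a wholly booster-driven direct effect about 23% of the time. These figures assume a 20% control rate, no covariates, equal arms and a normal approximation.

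The inherited block fixed effects are a further risk that depends on block size: inflation of about twofold in pairs, one third at four, 14% at ten and negligible at fifty or more.

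It does not follow that any hypothesis test is compromised. The analysis is labelled exploratory, and H1-2, H2 and H3-2 are unaffected.

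**What to change.** Base the conclusion about boosters on two linear models, with a primary-dose indicator and a booster indicator as outcomes. Fit both on the full randomised sample for each hypothesis, redefining the outcome and dropping nobody, with the same blocks, covariates and robust or clustered standard errors as H1-2, H2 and H3-2. Report each risk difference with a confidence interval. If each person is counted once and under one dose type, the two sum to the pooled effect.

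Estimate the two models jointly to test their difference. Because the right-hand sides are identical, regressing (primary indicator − booster indicator) on the same terms gives that difference and its standard error directly.

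If the multinomial model is kept, describe its Wald test as one of equal relative increases, and replace the block dummies with household-size strata. State in the dose-specific analyses that the outcome is redefined and all subjects are retained.

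The cost is small: the same data, a simpler model, and one exploratory test changed.
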